## Aims

The primary aim of this study is to assess if an audio program that has theta and delta BBFs arranged in an order that mimics a healthy adult hypnogram will improve sleep quality as evidence by an increase in sleep efficiency score when compared to a control group and no intervention. The author hypothesizes that when similar participants are matched and compared, those using BBF will have similar outcomes.

Based on the findings of the primary aim, the secondary aim of this study is to map out a plan for a series of future feasibility studies to support the development of a customizable all-night audio program to induce sleep, sustain sleep and provide a structure waking for persons with poor sleep quality (Figure 3).

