#### Cohort 1 (n 106) unblinded

Group 1: Baseline → theta/delta BBF alone → 1 week break → music aloneGroup 2: Baseline → music alone → 1 week break → theta/delta BBF alone

Since the participants in Cohort 1 will know when they are receiving the intervention, it could be argued that their outcomes are due to a placebo effect, therefore a second cohort using a different group of participants will be used.

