#### Cohort 2 (n 62) blinded

Group 3: Baseline → music alone → 1 week break → music embedded with theta/delta BBFGroup 4: Baseline → Music embedded with theta/delta BBF → 1 week break → music alone

Upon completion of both cohorts, a matched group analysis will be conducted to assess the differences between no intervention vs. music alone vs. theta/delta BBF alone vs. music embedded with theta/delta BBF.

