### Intervention

Three audio files will be used as the interventions: (1) music alone, (2) BBF alone, and (3) music with BBF. Using an example of a normal healthy adult sleep hypnogram as a model (Figure 2), a brainwave frequency algorithm will be created to reflect brainwave time points and duration (Table 1). The algorithm will then be used to generate dichotic tones to create theta and delta BBFs using *Adobe Audition software*. For example, to create a 6 Hz (theta BBF), a 230 Hz tone track will be generated for the left ear and a 236 Hz tone track will be generated for the right ear and played at the same time. A mini audio segment containing the two tracks made for each BBF will be placed into its correct order and time duration. The segments will then be stitched together to create a succinct 90-min audio file as REM sleep often begins at the 90-min mark. The audio will start with no BBF and will gradually incorporate theta BBF to delta BBF. Five-six 90-min audio tracks will be stitched together with each intro (no BBF) extended by 10–20% to replicate the increase of REM sleep as the night progresses. To create the music with BBF audio file, the BBF audio file will be layered onto a stereo music file (*Natural Healing Society's “100 Royalty Free Meditation and Ambient Songs”*) that has been stitched together to play for a continuous 8 h. The music audio files use textural layers of sound that include nature soundscapes, acoustic instruments such as the piano, strings and flute emulated through a synthesizer. Nature Healing Society's music was chosen because of their inventory of 432 Hz, 528 Hz, and Solfeggio frequency music. A *Soundcraft Signature 12 MDK mixing desk* will be used to balance decibels, to remove artifacts, fade BBF changes, and to set BBF levels to 20–30% below the volume of the carrier sound to minimize detection. Each intervention will be loaded onto a designated *Hotechs 32GB Memory MP3 player* and set to play in a continuous loop until the listener presses stop. The audio will be delivered through *SleepPhones*, a specialized headphone that wraps around the head which contains adjustable left and right speakers. The speakers are connected to one wire which runs down the back of the head and neck as to not to obstruct sleep. All equipment and music are marketed to the general public and have had no safety issues reported to date.

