### Power analysis and data analysis plan

For Cohort 1, since the study is comparing three measures, a 2 × 3 mixed ANOVA (between and within subject factor) will be used. The parameters for this analysis were as follows: (1) power of 1—β = 0.85, (2) level of significance of α = 0.05, (3) an autocorrelation parameter (i.e., average correlation) ranging from 0.3 to 0.7 (in increments of 0.2), and (4) a standardized effect size (F) ranging from small (0.1) to medium (0.25) in 0.05 increments. Using GPower software, the sample size estimates range from *n* = 52 (when the correlation of the repeated measures = 0.7 and the standardized effect size is *F* = 0.25) to *n* = 116 (when the correlation of the repeated measures = 0.3 and the standardized effect size is *F* = 0.1). For this study a sample of 106 will be sufficient (84 required, plus 25% for attrition bringing the total to 105 and the addition of 1 to make both arms equal in number).

For Cohort 2, assuming there is no difference in mean sleep efficiency score (i.e., mean difference = 0) between the interventions (BBF only, music with BBF) a sample size of 61 participants (plus 1 to make group equal in number *n* = 62) would be needed to declare with at least 80% power that the intervention effect in BBF only is the same as in music with BBF. Given that Cohort 1 is *n* = 106 and that propensity score matching with replacement will be implemented to make the groups comparable, the final test for intervention effect will be carried out with a power in excess of 80%.

For this two-period 2-arm cross-over design where each subject gets both treatments and repeated outcome measurements over time, a linear mixed model with repeated measures (MMRM) approach will be used. Unless otherwise stated, all statistical tests will be 2-sided with the probability of a Type I error not to exceed 0.05. Descriptive statistics will be used for all quantitative and qualitative variables at all data collection points. Continuous variables will be tabulated using N, mean, standard deviation or standard error (as appropriate), median, minimum, and maximum values. For categorical variables, frequency counts and percentages will be presented.

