For the match group analysis between Cohorts 1 and 2, propensity score matching will be implemented to construct a sample of subjects which have similar baseline covariate distributions between the cohorts. A logistic regression model, with intervention cohort as the dependent variable, will be employed to estimate the conditional distribution of the intervention given the covariates. The predictors in this model are baseline characteristics believed to be related to the main study outcome of interest (e.g., sleep efficiency score). To make optimal use of the number of subjects enrolled in Cohort 1, a match and replace method will be used whereby a BBF embedded with music user could be matched to more than one BBF only user. This will help maximize the number of matched BBF participants while enhancing the ability of the study to detect a difference in intervention between the two cohorts if indeed there is one.

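### The powered cross-cohort comparison changes music and blinding together, so neither similarity nor difference can be attributed; open versus blinded music alone is an unused supportive contrast.

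*Protocol article*

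**What the plan says.** All places are in the protocol article.

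- **Design.** The study design section sets up "Cohort 1 (n 106) unblinded", which hears BBF alone and music alone in crossover, and "Cohort 2 (n 62) blinded", which hears music alone and music with BBF in crossover. The Cohort 1 subsection gives the reason for the second cohort: because Cohort 1 participants know what they receive, "it could be argued that their outcomes are due to a placebo effect, therefore a second cohort" of different people is added.
- **Audio.** Under Intervention: "Three audio files will be used as the interventions: (1) music alone, (2) BBF alone, and (3) music with BBF". One music-alone file thus serves both cohorts.
- **Hypothesis.** Under Aims, the author expects that after matching "those using BBF will have similar outcomes".
- **Powered cross-cohort test.** Under Power analysis and data analysis plan, 61 participants (62 enrolled) are needed to "declare with at least 80% power that the intervention effect in BBF only is the same as in music with BBF". Matching is by propensity score with replacement, "whereby a BBF embedded with music user could be matched to more than one BBF only user".
- **Other comparisons.** The Cohort 2 subsection lists a four-way matched comparison in which music alone is a single level. The Abstract names Cohort 1's music as the control. The final mixed model lists intervention, period and sequence as fixed effects and names no cohort or blinding term.
- **Allocation.** Under Screening, consenting, and randomization process, participants are randomised to cohort and then to group.

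**The concern.** Both arms of the powered cross-cohort test contain BBF. What differs is whether music is present, whether the listener knows the treatment, and how the BBF is delivered (alone, or layered under music at reduced level). One difference in means cannot be divided among three causes. A verdict of sameness could mean that none of them matters, or that a gain from music is offset by a gain from open-label expectation. A verdict of difference is equally ambiguous. At stake is the interpretation of the only between-cohort result for which a sample size was set.

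The Abstract's choice of control raises the same difficulty: blinded music with BBF against open music changes BBF and blinding together.

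Meanwhile the music-alone file is the only audio heard under both blinding conditions. The article describes no comparison of the two.

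**Working it through.** **1. What each contrast estimates.** Assume additive effects on sleep efficiency: b for BBF alone, b′ for BBF embedded in music, m for music, e_open for expectation when the listener knows BBF is playing, e_blind for expectation when BBF is possible, and e_known for expectation when the listener knows it is only music.

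| Contrast | Terms | Result |
|---|---|---|
| Planned: open BBF only − blinded music with BBF | (b + e_open) − (b′ + m + e_blind) | (b − b′) + (e_open − e_blind) − m |
| Within Cohort 2: music with BBF − music | (b′ + m + e_blind) − (m + e_blind) | b′ |
| Unused: blinded music − open music | (m + e_blind) − (m + e_known) | e_blind − e_known |

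**2. Illustration of the planned contrast.** Take b = b′, e_open − e_blind = 2 points and m = 2 points. The result is 0 + 2 − 2 = 0, for b = 0 and for b = 5 alike. In SD units, if music adds 0.3 and open knowledge adds 0.5, music with BBF minus BBF only is 0.3 − 0.5 = −0.2, and music appears harmful. These values are assumptions that show the mechanism; the article gives none.

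**3. Why matching does not help.** Blinding is fixed by cohort. Every matched pair has one open and one blinded member, whatever the baseline covariates.

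**4. The plan's own figure.** The 61 participants cannot be reproduced because the article prints neither an equivalence margin nor an SD. Back-solving from two one-sided tests at 0.05, 80% power and a true difference of 0, margin/SD = (1.645 + 1.282) × √(1/n₁ + 1/n₂):

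- 61 vs 61: 2.926 × 0.181 = 0.53 SD
- 61 vs 106: 2.926 × 0.161 = 0.47 SD
- 61 pairs: 2.926/√61 = 0.37 SD of the paired difference

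On any of these readings, music or expectation effects of several tenths of an SD could sit inside the margin or cancel.

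**5. Precision of open versus blinded music.** Each participant contributes one music period. SE = SD × √(1 − r²) × √(1/n₁ + 1/n₂), and half-width = 1.96 × SE. The n come from the article; SD and r are assumptions.

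| SD (points) | r | n₁ vs n₂ | SE | 95% half-width |
|---|---|---|---|---|
| 8 | 0.5 | 106 vs 62 | 8 × 0.866 × 0.160 = 1.11 | 2.2 |
| 6 | 0.7 | 106 vs 62 | 6 × 0.714 × 0.160 = 0.69 | 1.3 |
| 10 | 0.5 | 80 vs 47 (25% loss) | 10 × 0.866 × 0.184 = 1.59 | 3.1 |

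In the base case, power to detect 2 points is Φ(2/1.108 − 1.96) = Φ(−0.155), about 44%. The difference detectable with 80% power is 0.39 SD, or 3.1 points at SD 8.

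**6. Carryover check.** In period 2, Group 1 hears music after BBF alone and Group 4 hears it after music with BBF, so any carryover differs by cohort. In period 1, Group 2 (106/2 = 53) and Group 3 (62/2 = 31) hear music with no earlier audio. With SD 8 and r 0.5, SE = 6.93 × √(1/53 + 1/31) = 6.93 × 0.226 = 1.57, half-width 3.1 points.

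**The case against.** The strongest reply is that Cohort 2 already does what it was added for. Its blinded crossover isolates the embedded BBF effect from expectation (second row of the first table), and the mixed model analyses it. This stands. A reader might infer that the design leaves the placebo question open; it does not.

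A reader might also infer that the author treats similarity of BBF only and music with BBF as evidence against placebo, since the placebo motive (Cohort 1 subsection) and the similarity hypothesis (Aims) appear in one article. No sentence joins them. Read on its own terms, the matched analysis compares two ways of delivering BBF, and that the BBF effect largely cancels there is expected. This stands too, but even that narrower purpose is compromised, because blinding changes along with delivery form.

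Third, the music contrast is tempting to present as a clean isolation of expectation, or as a lower bound on open-label bias. The documents do not support either. It captures possible BBF against known music only, may include disappointment at knowingly hearing the comparator, and is open to differential carryover in period 2. A lower bound would also need belief to act monotonically, which nothing in the article establishes.

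Finally, this is a condensed article and need not list every secondary contrast. That is fair as to the missing music contrast. It does not touch the main point, which concerns a comparison the article itself specifies and powers.

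**Conclusion.** The point holds as a limit on interpretation. The powered cross-cohort comparison confounds music, blinding and delivery form, and baseline matching cannot undo this. The algebra assumes additivity, but the confounding itself does not depend on it. Exact cancellation to 0 is a special case; the general problem is that a difference of any size cannot be attributed.

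The conclusion about BBF against placebo rests safely on the blinded contrast within Cohort 2. The music contrast adds useful but imprecise information: a half-width of about 2.2 points in the base case, 1.3 to 3.1 over SD 6 to 10, r 0.5 to 0.7 and 0 to 25% loss. A null result would not exclude a small expectation effect. Its standing as a randomised comparison relies on the article's statement that participants are randomised to cohort.

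**What to change.** 1. State that the conclusion on BBF against placebo comes from music with BBF minus music alone within Cohort 2.
2. State that similarity or difference between BBF only and music with BBF across cohorts is not interpretable as evidence for or against a placebo effect, and that music, blinding and delivery form all change in that comparison.
3. Pre-specify one supportive contrast for sleep efficiency and PSQI: blinded music alone (Groups 3 and 4) minus open music alone (Groups 1 and 2). A model with one record per participant, containing cohort, baseline and period, is enough.
4. Repeat it in period 1 only, Group 3 against Group 2, as a check on differential carryover.
5. Report both with confidence intervals as the effect of believing one may be receiving BBF versus knowing one hears only music, not as a full measure or guaranteed lower bound of open-label bias. Show alongside them the Post-Study Questionnaire item on whether Cohort 2 participants could tell they were receiving BBF.

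The cost is two model contrasts and a few sentences. No new participants, visits or measurements are needed. The drawback is the limited precision, most marked in the period-1 check (half-width about 3.1 points at SD 8 and r 0.5).

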### Study procedure

#### Screening, consenting, and randomization process

Once the participants have been screened using the inclusion and exclusion criteria, they will sign an Institutional Review Board approved consent and randomized into two cohorts using block randomization. This process was chosen as it reduces bias and increases the probability that the group in each cohort will contain an equal number of individuals (4). Participants in Cohort 1 will then be randomized into Groups 1 or 2 while participants in Cohort 2 will be randomized into Groups 3 or 4.

#### Initial appointment

Participants will be asked to complete the Participant Demographic Sheet and PSQI questionnaire. At the completion of the appointment, each participant will be given:

1) Sleep actigraphy monitor.2) Instructions on how and when to complete the National Sleep Foundation sleep diary questionnaire that they will receive daily *via* email. Participants will be instructed to complete diary entries within 24 h of receipt. Data will be uploaded anonymously in real-time to the online survey dashboard.3) One MP3 player pre-loaded with the designated audio file based on group assignment.4) One set of SleepPhones stereo headphones to work in conjunction with the MP3 player. If a participant experiences discomfort with the SleepPhones, personal headphone or earbuds may be used at his or her own risk as long as it emits stereo sound and does not have noise canceling technology.

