#### National Sleep Foundation sleep diary (version 6)

The National Sleep Foundation Sleep Diary is a short 15-item questionnaire that captures the daily habits that may influence sleep. The questionnaire is divided into two parts, seven questions to be completed upon awakening and eight questions to be completed at bedtime. Given that most of the questions upon awakening will be captured by the actigraphy monitor, these questions will not be utilized for the study. As for the questions to be completed at bedtime, these address: (1) exercise, (2) medication use, (3) napping, (4) sleepiness during the day, (5) mood, (6) alcohol, food and caffeine intake, (7) timing of caffeine intake, and (8) bedtime routine. This instrument is not scored but will be used to assess patterns and if those patterns affected the sleep outcomes (38). According to the literature, it is recommended that persons wearing actigraphy monitors also use a sleep diary as it captures subjective data that an actigraphy monitor cannot detect (39).

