#### Final appointment

The participant will be scheduled to return all equipment. The investigator will check the online survey dashboard to ensure that all sleep diaries have been completed. Participants will then complete the PSQI for Intervention 2 and Post-Study Questionnaire (Table 2).

**Table 2 T2:** Data collection procedure.

**Action**	**Initial appointment**	**Weeks 1 and 2**	**Weeks 3 and 4**	**2nd appointment**	**1 week break**	**Weeks 6 and 7**	**Final appointment**
Screening, consent and randomization	X						
Participant demographic questionnaire	X						
National Sleep Foundation sleep diary		X	X		X	X	
Philips Actiwatch Spectrum Pro actigraphy monitor		X	X		X	X	
MP3 player with intervention 1			X				
MP3 player with intervention 2						X	
Pittsburgh Sleep Quality Index	X			X			X
Post-study questionnaires							X

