### Outcomes measures

The primary aim of this study is to assess if an audio program that has theta and delta BBFs arranged in an order that mimics a healthy adult hypnogram will improve sleep quality. To subjectively measure improvement in sleep quality, the PSQI total scores from Interventions 1 and 2 will be compared to baseline to note any statistically significant differences. This score will also be correlated with the sleep efficiency percentage scores taken from the sleep actigraphy monitor as a secondary validation. To objectively measure improvement in sleep quality, sleep efficiency percentage calculated from the sleep actigraphy monitor will be used. Even though 80 to 85% is considered good sleep efficiency, improvement in sleep efficiency will be determined by identifying any statistically significant changes when compared to the participant's baseline where there was no intervention. Sub measures of sleep efficiency such as sleep latency, number of minutes awake after sleep onset, and number of times awaken throughout the night will be analyzed individually. Data collected from the National Sleep Foundation Sleep Diary will be assessed to see if there are any relationships between exercise, medication use, napping, sleepiness during the day, mood, alcohol, food and caffeine intake, timing of caffeine intake, and bedtime routine and the various sleep outcomes. The Post-Study Questionnaire will be used for informational purposes to assess the participants' experience, perception of the technology, and the feasibility of conducting Phases 3 and 4.

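### The 24 h diary window does not hold the bedtime questions to bedtime, so mood and sleepiness can be recorded after the night they are meant to explain

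*Protocol article*

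**What the plan says.** All references are to the protocol article.

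- **National Sleep Foundation sleep diary (version 6).** The diary has "seven questions to be completed upon awakening and eight questions to be completed at bedtime". Because actigraphy covers most of the awakening items, "these questions will not be utilized for the study". That leaves the bedtime items, which include napping, daytime sleepiness, mood and caffeine. The section says they serve to show whether a participant's patterns affected the sleep outcomes.
- **Initial appointment.** Participants receive "Instructions on how and when to complete the National Sleep Foundation sleep diary questionnaire that they will receive daily" by email. The next sentence reads: "Participants will be instructed to complete diary entries within 24 h of receipt". Entries are uploaded anonymously and in real time to a survey dashboard. The hour of the email is not given.
- **Outcomes measures.** The diary data "will be assessed to see if there are any relationships between exercise, medication use, napping, sleepiness during the day, mood" and the remaining items, on one side, and the sleep outcomes on the other.
- **Power analysis and data analysis plan.** Diary entries are summarised by data collection time point, and diary items may be added to the model as covariates to improve precision.
- **Final appointment.** The investigator checks the dashboard to "ensure that all sleep diaries have been completed". No criterion of timeliness is attached.

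**The concern.** The diary's role in this plan depends on order in time: the habit or state comes first and the night follows. The diary section respects that order by keeping only the items with "eight questions to be completed at bedtime". The rule given to participants does not secure it. An entry made the next morning or afternoon complies with the 24 h window, yet by then the participant knows how the night went.

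The effect differs by item. Mood and sleepiness are states, and a poor night can change the answer directly. Napping, caffeine, exercise, alcohol and routine are events of the preceding day. A late answer on these mainly adds recall error, or describes the day after the night by mistake.

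At stake is how the diary relationships are read. A poor night that causes low mood the next day could be reported as low mood that impaired sleep. Used as a covariate, such an item is partly a consequence of the outcome it adjusts, so it no longer offers a clean gain in precision. If on-time and late entries are pooled without their timing, the direction cannot be recovered afterwards.

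**Working it through.** The plan gives no figure on this point to reproduce. The check is clock arithmetic followed by a comparison of the passages.

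**Inputs**
- Window: 24 h from receipt (Initial appointment).
- Email time: not stated, so varied below.
- Night length S: an assumption. 8 h matches the length of the audio file (Intervention), and 6 h is the lower end of the range.
- Clock times of 23:00 for bed and 07:00 for rising: assumptions.

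**Formula.** If the email arrives t hours before bedtime, the window closes 24 − t hours after bedtime, which is 24 − t − S hours after waking. It stays open past waking whenever t < 24 − S.
- S = 8 h: t < 16 h.
- S = 6 h: t < 18 h.

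**Results for S = 8 h, bed 23:00, rising 07:00**

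| Email at | t (h) | Open after waking: 24 − t − 8 (h) | Share of permitted waking time that follows the night |
|---|---|---|---|
| 08:00 | 15 | 1 | 1/16 = 6% |
| 12:00 | 11 | 5 | 5/16 = 31% |
| 18:00 | 5 | 11 | 11/16 = 69% |
| 21:00 | 2 | 14 | 14/16 = 88% |

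The denominator is t waking hours before bed plus 24 − t − 8 after it, always 16. The last column shows opportunity. It does not estimate how many entries will be late.

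**Exception.** An email arriving during the previous sleep period closes before waking. At 03:00, for example, t = 20 and the window ends 4 h after bedtime. The actigraphy section expects some participants to work varying shifts and sleep by day, so a single sending hour would not meet this exception for everyone.

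**What late entry could do to a same-night correlation.** Suppose the true bedtime state is unrelated to the night, the next-day state correlates r with it, a share p of entries is late, and every late entry reports the next-day state. The pooled correlation is then about p × r:
- p = 0.25, r = 0.3: 0.075
- p = 0.5, r = 0.3: 0.15
- p = 0.5, r = 0.5: 0.25

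Neither p nor r has a source in the documents. These values show the mechanism and do not forecast its size.

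**Passages side by side.** The diary section fixes bedtime as the time of completion, and the Initial appointment section allows 24 h. Nothing in the article restricts entry to before sleep, marks late entries, or says which night an entry belongs to. The final check looks at completeness only.

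**The case against.** The strongest reply is that the 24 h rule is only an outer deadline for submission. The diary section still says bedtime, and the sentence before the rule promises instructions on how and when to complete the diary. Those instructions are not shown, and a journal article may leave them to the full protocol. This stands in part: the article does not expressly withdraw bedtime completion. But 24 h is the only timing rule it gives as an instruction to participants, and it does not say that 24 h is merely a deadline.

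A second reply is that same-night pairing is assumed. This also stands. If diary and sleep data are averaged over a two-week phase, on-time entries already contain the next-day response to 13 of the 14 nights, and uniformly late entries contain all 14. Late entry then changes almost nothing, and correcting the timing would not recover direction either. The concern applies where entries are tied to individual nights.

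Some stronger readings are tempting, and the documents do not support them:
- **Every window spans the coming night.** An overnight email is the counter-example above.
- **Diaries will be back-filled weeks later because of the final check.** That would breach the 24 h rule. The check mentions no retrospective entry, and the Weeks 3 and 4 section says missing data will not be recaptured, although in the context of monitor failure.
- **All items are equally open to reverse effects.** The route is direct for mood and sleepiness. For the other items the main risk is recall or wrong-day error.
- **With 168 × 49 = 8,232 diary nights, even a trivial spurious correlation would be significant.** That count assumes every participant supplies every night. It also ignores clustering within participants, whom the plan models with a random effect.

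**Conclusion.** The point holds as a mismatch between the stated timing of the diary items and the stated completion rule. For any email received in waking hours, an entry made within the rule can postdate the night it is meant to explain. Mood and sleepiness can then be reverse effects, and the other items can be misrecalled or assigned to the wrong day.

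The size of any bias is unknown, because the email time, the share of late entries and the pairing of entries with nights are not given. The conclusion assumes a main sleep period of about 6 to 8 h. For the reverse effect, it also assumes that entries are related to the same night's actigraphy or used as covariates at that level. Sleep efficiency from actigraphy, the main indicator, is affected only if diary items enter its model. The matter deserves correction before data collection, but it does not threaten the primary comparison in itself.

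**What to change.** Reconcile the diary section with the Initial appointment section:

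1. Instruct participants to complete the diary at bedtime, before trying to sleep.
2. Send the email shortly before each participant's usual bedtime, with its own sending time for day sleepers.
3. Keep 24 h, if at all, only as an outer limit for submission.
4. Record the upload time. An entry made after that night's actigraphic bedtime is excluded from that night's diary-sleep analysis, or analysed separately.
5. State which night each entry is paired with.

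The cost is small: a changed instruction, a timed email, and some more missing diary entries for the night concerned. One condition must be met. Uploads are described as anonymous, so the upload time has to be linkable to the participant's study code. Relating diary entries to a participant's actigraphy needs that link anyway. The actigraphy data are unaffected.
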